#### Client Quantitative Outcome Measures

All primary and secondary outcomes will be assessed over the phone at baseline, 4-, and 8-weeks (primary study endpoint):

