##### Primary outcome

*The Perceived Stress Scale (PSS)* is a validated and commonly used measure of stress (28). The 14-item scale assesses the degree to which life events are appraised as stressful. It asks respondents about how often they have felt certain ways in the past month, with responses ranging from 0 (never) to 4 (very often).

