### Data Analysis

#### Quantitative Analysis

Descriptive statistics for continuous variables will include means and standard deviations, while categorical variables will be summarized using frequencies and proportions. A within-subjects repeated measure analysis of variance (ANOVA) will be conducted for the PSS (primary outcome), COVID Fear Scale, PHQ-9, GAD-7, and mental healthcare utilization (secondary outcomes) to assess differences in measures between baseline and the 8-week follow-up between groups with different baseline risk (low, medium, and high risk). Additional analysis of covariance (ANCOVAs) will control for variables that differ between groups at baseline. We will use LOCF to handle missing data that results from study attrition. Although we have found it extremely rare to be missing baseline data when, for example, a participant answers all but one question on a measure, in any such case we will exclude the participant's data for that measure. All ANOVAS will be tested at two-tailed alpha = 0.05. Linear mixed effect regression models, adjusting for age and sex, will analyze the effect of TIP-OA on all outcomes (PSS, COVID Fear Scale, PHQ-9, GAD-7, and mental healthcare utilization) collected at baseline and 8-week follow-up. We will perform additional linear mixed effect regression models accounting for a larger group of important variables such as client referral source (e.g., referred from clinic vs. self-referred) and cognitive functioning (e.g., suspected mild dementia vs. no suspected mild dementia) on mental health outcomes. Variable selection in linear mixed effect model (32) will be used to select important fixed effect covariates as they relate to the outcome. The fixed effect point estimates and corresponding confidence intervals and *p*-values will be computed. Additional subgroup analyses will also compare the primary outcome (PSS) between important subgroups [e.g., referral source (referred from clinic vs. self-referred) and cognitive functioning (suspected mild dementia vs. no suspected mild dementia)]. Analyses will be run using R statistical software.

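### Carrying the last score forward for clients who drop out biases the week-8 change in perceived stress, in a direction and by an amount the protocol cannot fix in advance

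*Protocol article*

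**What the plan says.** Under Client Quantitative Outcome Measures, outcomes "will be assessed over the phone at baseline, 4-, and 8-weeks (primary study endpoint"). The primary outcome is the PSS.

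Under Quantitative Analysis, a repeated-measures ANOVA is used "to assess differences in measures between baseline and the 8-week follow-up between groups with different baseline risk (low, medium, and high risk"). ANCOVAs follow, and then the attrition rule: "We will use LOCF to handle missing data that results from study attrition". The next sentences cover partly answered baseline scales and the test level ("All ANOVAS will be tested at two-tailed alpha = 0.05"). After that come linear mixed models adjusted for age and sex, which "will analyze the effect of TIP-OA on all outcomes (PSS, COVID Fear Scale, PHQ-9, GAD-7, and mental healthcare utilization) collected at baseline and 8-week follow-up". Confidence intervals are promised for the fixed effects of the mixed models.

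The LOCF sentence is not confined to the ANOVAs. No multiple imputation and no sensitivity analysis for missing data is named. The mixed models are not said to use un-imputed data.

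**The concern.** With three visits, LOCF has only two possible effects on a missing week-8 score. A client lost before week 4 receives the baseline score, so the change is exactly zero. A client lost between weeks 4 and 8 receives the week-4 score. The reported change then mixes 8-week change, 4-week change and zeros, in proportions set by when clients happened to leave.

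That mixture equals the week-8 change only if mean stress at the carried visit is the same as at week 8 and leaving is unrelated to stress. The article gives reasons for doubt. It hopes for an effect on stress, expects a second wave of infection in the fall of 2020 (Introduction), and accepts that clients may move between risk categories during the 8 weeks (Strengths and Limitations). Referral sources include COVID-19 inpatient units, geriatric psychiatry and long-term care, where leaving through illness is plausible, though the article does not say so. There is no control group in which a similar bias might partly cancel.

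At stake are the estimate of PSS change, any interval computed from carried-forward data, and the low/medium/high risk comparison.

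**Working it through.** **From the document.** 200 clients (Selection/Treatment of Subjects); visits at baseline, week 4 and week 8; the baseline-to-week-8 contrast; two-sided alpha 0.05. There is no plan figure to reproduce, because Sample Size Justification gives no effect size, SD, power or dropout rate.

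**Assumed.** PSS SD 8; correlations 0.7 (baseline to week 4), 0.7 (week 4 to week 8) and 0.55 (baseline to week 8); true mean change D4 = -1.5 and D8 = -3.0.

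**Step 1: mean under LOCF, random dropout.** Let d be the fraction lost and b the share of losses before week 4:

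m = (1-d)·D8 + d(1-b)·D4 + d·b·0

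With b = 0.5:
- d = 0.10: 0.90(-3.0) + 0.05(-1.5) = -2.775, about -2.8
- d = 0.23: 0.77(-3.0) + 0.115(-1.5) = -2.48, about -2.5

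**Step 2: standard error and coverage.** The change variances are V8 = 2·64·(1-0.55) = 57.6 and V4 = 2·64·(1-0.7) = 38.4. The mixture variance is (1-d)(V8 + D8²) + d(1-b)(V4 + D4²) - m².
- d = 0.10: 0.90·66.6 + 0.05·40.65 - 7.70 = 54.27; SE = √(54.27/200) = 0.521. Bias/SE = 0.225/0.521 = 0.43. Coverage = Φ(1.96-0.43) - Φ(-1.96-0.43) = 0.93.
- d = 0.23: 0.77·66.6 + 0.115·40.65 - 6.16 = 49.79; SE = 0.499. Bias/SE = 0.5175/0.499 = 1.04. Coverage = 0.82. Simulation gives 0.81.

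**Step 3: stress-related dropout (simulation).** When more-stressed clients are likelier to leave and 27% are missing, LOCF gives about -1.9 with coverage about 0.4. It freezes high scorers at their high scores and never sees their later fall. The result depends on the assumed strength of that link.

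**Step 4: is the SE itself wrong?** In simulation the mean reported SE was 0.496 against a sampling SD of 0.510 for the LOCF estimator (23% random dropout). With no true change the figures were 0.492 against 0.488, with coverage 0.951. The SE is about right for the estimator used, so the undercoverage comes from bias.

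**Step 5: direction.** If benefit fades (D4 = -4, D8 = -2) and all losses follow week 4, m = (1-d)(-2) + d(-4) = -2.2, -2.4 and -2.6 at 10, 20 and 30%. Benefit is now overstated. If D4 = D8 and losses are random and all after week 4, there is no bias.

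**Step 6: risk-group test.** Take SD 8, correlation 0.6 between all visits, groups of 67/67/66, equal true change of -3 in every group, and all losses before week 4.
- Dropout 10/20/30% by group: expected LOCF changes are -2.7/-2.4/-2.1; simulated type I error is about 0.07-0.08.
- Dropout 5/20/40%: expected changes are -2.85/-2.4/-1.8; type I error is about 0.12.
- Observed week-8 data only: about 0.04-0.06.

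**Step 7: overall test of no change.** Under the Step 6 assumptions for SD, correlation and loss timing, and 20% dropout, LOCF gives -2.40/0.460 = -5.2, against -3.0/0.566 = -5.3 from observed data. This test is barely affected.

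**The case against.** The strongest case on the other side has four parts.

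**The size is unknown.** This stands. Dropout, SD, correlations and trajectory are all assumed. At 10% random dropout the bias is about 0.2 points and coverage is 0.93. The coverage near 0.4 belongs to one assumed dropout mechanism and is not a property of this plan.

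**The interval.** A reader might infer that counting copied scores as data makes the standard error too small. The check does not support that: the reported SE agrees with LOCF's own sampling variability. It is smaller than the SE of a likelihood analysis, but that is a different estimator. It is also unsettled which intervals are touched. Intervals are promised only for the mixed models, and the LOCF sentence sits among the ANOVA sentences. Reading LOCF as applying to the ANOVAs alone is plausible, but the text does not say so.

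**Utilization.** A reader might infer that pre-baseline visit counts will be copied into follow-up. Secondary outcomes takes utilization from medical records over fixed 8-week windows, so loss of phone contact need not create a gap. Only a clarifying sentence is needed.

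**Partly answered baseline scales.** For these the plan says "in any such case we will exclude the participant's data for that measure". That is a separate, transparent rule for cases the article describes as very uncommon. It has no bearing on attrition.

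The study is also uncontrolled, which the article names as its main limitation. That limits causal claims, but it does not excuse an avoidable bias in the change being reported.

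**Conclusion.** The point holds as a bias in the estimate. LOCF is the only stated rule for attrition, nothing withdraws it, and with these visits it replaces a missing 8-week change with zero or with the 4-week change. The PSS change is biased unless the carried-visit mean equals the week-8 mean and dropout is unrelated to stress. The risk-group comparison is exposed when dropout differs by risk group.

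Neither the direction nor the size can be read from the document. In the assumed scenarios with a true change of -3.0, the LOCF estimate runs from about -2.8 to about -1.9. A fading benefit reverses the sign of the error. The documents do not support saying that LOCF always understates benefit, that the standard error is miscalculated, or that the overall test of no change is invalid.

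**What to change.** - Delete the LOCF sentence.
- Analyse the PSS and the other scales with the linear mixed model already planned, fitted to all observed baseline, week-4 and week-8 scores, with visit categorical and no imputation. This is valid when dropout depends only on observed data, and it brings the week-4 scores into the model.
- Take the risk-group comparison from the visit-by-risk-group term of that model.
- Add one delta-adjusted sensitivity analysis for dropout not at random.
- State that LOCF does not apply to utilization taken from records.

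**Cost.** Wording and slightly more analysis; the visits are already scheduled. The interval will be somewhat wider: under the Step 1 assumptions with 25% random dropout, the SE is about 0.61 for the likelihood analysis against 0.49 for LOCF.

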### Selection/Treatment of Subjects

The first 200 TIP-OA clients who provide informed consent will participate in data collection for research.

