##### Secondary outcomes

*The COVID Fear Scale* is an 18-item scale measuring individuals' anxiety, fear, and concern surrounding the COVID-19 pandemic. Items include: “Fear that I will be infected” and “Worry if I will be assigned to COVID wards if hospitalized” (29). The *Patient Health Questionnaire-9 (PHQ-9)* is a 9-item self-report questionnaire used to assess depressive symptom severity. The questionnaire asks individuals how often in the last 2 weeks they have been bothered by problems like “feeling down, depressed, and hopeless” and “poor appetite or overeating.” Scores for each question include 0 (not at all), 1 (several days), 2 (more than half of the days), and 3 (nearly every day) (30). The *Generalized Anxiety Disorder 7-Item Scale (GAD-7)* is a brief scale that measures symptoms of anxiety present in the previous 2 weeks. Respondents' scores can range from 0 (not at all sure) to 3 (nearly every day). Items include “Not being able to stop or control worrying” and “Being so restless that it's hard to sit still” (31). *Mental healthcare utilization* will be assessed using medical records, including the number of ER visits, hospitalizations, and outpatient visits (1) in the 8 weeks prior to baseline and (2) during 8-week follow-up.

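### Change in mental healthcare utilization, a visit count, is compared across risk groups by an equal-variance ANOVA whose error rate can lie far above or far below the stated 5%.

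*Protocol article*

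**What the plan says.** **Outcome.** Under Secondary outcomes, mental healthcare utilization "will be assessed using medical records, including the number of ER visits, hospitalizations, and outpatient visits", counted "in the 8 weeks prior to baseline and (2) during 8-week follow-up". Each client therefore contributes two counts over windows of equal length.

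**Risk-group comparison.** Under Quantitative Analysis, the outcome list of the within-subjects repeated-measures ANOVA ends with "GAD-7, and mental healthcare utilization (secondary outcomes) to assess differences in measures between baseline and the 8-week follow-up between groups with different baseline risk". The stated level is "All ANOVAS will be tested at two-tailed alpha = 0.05".

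**Overall effect.** In the same section, linear mixed models adjusted for age and sex "will analyze the effect of TIP-OA on all outcomes (PSS, COVID Fear Scale, PHQ-9, GAD-7, and mental healthcare utilization"). No count model, transformation or robust variance is named for utilization in either analysis.

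**Sample.** "The first 200 TIP-OA clients who provide informed consent will participate in data collection for research". Risk is coded by clinicians as low, medium or high at screening. The article gives no group sizes, visit rates or variances.

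**Data source.** Client Quantitative Outcome Measures states: "All primary and secondary outcomes will be assessed over the phone at baseline, 4-, and 8-weeks". Utilization is listed among the secondary outcomes.

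**The concern.** The standard repeated-measures ANOVA pools one error variance over the three risk groups. For visit counts the variance grows with the mean. Risk is a clinician rating of mental-health risk and case complexity, and referral sources range from self-referral to a geriatric psychiatry clinic and COVID-19 inpatient units, so different visit rates by risk group are plausible. Consecutive enrolment does nothing to equalize group sizes. Unequal variance combined with unequal group size is the setting in which the ANOVA F test loses its level.

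At stake is the second study objective, comparison of outcomes by baseline risk, as it applies to utilization. A significant time-by-risk result could be noise if the high-risk group is small. A null result could be uninformative if that group is the largest. An additive model also cannot tell a common proportional change from a larger effect in high-risk clients, and the article does not say which kind of difference it means.

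**Working it through.** **Inputs from the article:** 200 clients, three risk groups, two equal 8-week windows, two-sided alpha 0.05. The sample-size section gives no effect size, SD or visit rate, so there is no power figure to reproduce. The only stated figure to check is the 0.05.

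**Assumptions (not in the article):** mean visits per 8 weeks in low/medium/high risk of 0.2/0.5/1.5, 0.5/1/3 or 0.5/1.5/4; group sizes as in the tables. Counts are Poisson with mean m·U·V, where U is a persistent client effect and V an occasion effect, each gamma with mean 1 and variance 1.

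**Step 1: form of the test.** With two time points, the time-by-risk F test equals a one-way ANOVA on change scores, with 2 and 197 df.

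**Step 2: variance of change.** Given U, each count has variance mU + m²U². As E[U] = 1 and E[U²] = 2, with no true change:

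Var(change) = 2(m + 2m²) = 2m + 4m².

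Rates 0.5/1/3 give variances 2, 6 and 42.

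**Step 3: what the F ratio compares.** With no true change,
- E[MS between] = ½ Σ(1 − nᵢ/200)σᵢ²
- E[MS within] = Σ(nᵢ − 1)σᵢ² / 197

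These should be equal if the test is to be calibrated.

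| Low/medium/high | E[MS between] | E[MS within] | Ratio |
|---|---|---|---|
| 67/67/66 | (1.33+3.99+28.14)/2 = 16.73 | (132+396+2730)/197 = 16.54 | 1.01 |
| 100/60/40 | (1.0+4.2+33.6)/2 = 19.40 | (198+354+1638)/197 = 11.12 | 1.75 |
| 120/60/20 | (0.8+4.2+37.8)/2 = 21.40 | (238+354+798)/197 = 7.06 | 3.03 |
| 20/60/120 | (1.8+4.2+16.8)/2 = 11.40 | (38+354+4998)/197 = 27.36 | 0.42 |

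A small high-risk group makes the pooled error too small; a large one makes it too big.

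**Step 4: simulated rejection rates, no change in any group, nominal 5%.** Ranges run over the assumed rates that rise with risk.

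| Low/medium/high | ANOVA time-by-risk |
|---|---|
| 67/67/66 | 6–8% |
| 100/60/40 | about 18% |
| 120/60/20 | 31–33% |
| 20/60/120 | about 0.5% |

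**Step 5: what is not a problem.** With equal rates in the three groups (0.5 or 1.5 visits), the same ANOVA rejects in about 4–6% for every split, although the counts are strongly skewed (skewness 4 to 5, 52–72% zeros). The overall pre/post comparison, simulated as a paired t test, also stays at about 4–6%.

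**Step 6: scale.** A 30% fall in every group is 0.30 × 0.5 = 0.15 visits at low risk and 0.30 × 3 = 0.9 at high risk. With rising rates the ANOVA then rejects in 2.7–39.5% of trials, and with a 50% fall in 13.8–55.5%, depending on split and rates.

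**Step 7: alternatives, no change.** A Welch test on change scores rejects in about 4–5%. A log-link test of equal rate ratios with uncorrected robust variance rejects in about 6–11%, and could not be computed in up to 7.8% of trials when the low-risk group had 20 clients at 0.2 visits each.

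**The case against.** The strongest reply is that every figure above rests on assumed rates and splits. With equal groups the ANOVA is only slightly off, and with a large high-risk group it is conservative. That stands: the documents do not fix the direction of the error. They also contain nothing that protects the level.

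Three stronger readings are tempting, and the documents do not support them.
- **That a skewed count in a normal-theory model produces false differences.** With about 200 clients, skewness alone leaves the error near 5%, and no visit rate is given that would show the counts to be low.
- **That the overall effect of TIP-OA on utilization is tested at the wrong level.** The overall pre/post comparison holds its level.
- **That detecting a common proportional fall is a false positive.** The absolute changes truly differ there. An absolute scale is legitimate, and the Discussion itself speaks of a reduction in the number of services requested. The fault is only that the scale is not stated.

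It can also be said that a condensed article leaves modelling detail to a fuller plan. That does not answer the point, because the article names the test for this outcome. It is fair to add that utilization is one of several secondary outcomes, that the more specific Secondary outcomes text probably governs the data source, and that a count model has costs of its own.

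**Conclusion.** The point holds in limited form. The protocol article explicitly assigns an equal-variance ANOVA to the change in a visit count across risk groups. If rates rise with risk and groups are unequal, the true error rate of that test can lie anywhere from about 0.5% to about 33% against a stated 5%. This rests on assumed rates, overdispersion and group sizes, none of which the article gives. The defect is confined to the time-by-risk comparison of one secondary outcome.

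The conflict over data source needs no assumption. Utilization cannot both be collected by phone at three visits and be taken from medical records in two windows. It is a separate wording matter and does not affect the error-rate argument. The correction should be made before analysis.

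**What to change.** 1. In Quantitative Analysis, take utilization out of the equal-variance ANOVA. Specify a heteroscedasticity-robust test of change by risk group, for example Welch on change scores or a model with robust or group-specific variance.
2. Report rate ratios from a log-link count model with a period-by-risk term: negative binomial, or Poisson GEE with small-sample-corrected robust standard errors and client as cluster.
3. State whether differences between risk groups are meant as absolute or proportional.
4. Give ER visits and hospitalizations separately, but descriptively where counts are sparse.
5. Reconcile Client Quantitative Outcome Measures with Secondary outcomes on how and when utilization is obtained.

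**Cost:** changed wording and slightly more analysis work; no new data. The rate-ratio model has a real downside: without small-sample correction its robust test is mildly liberal, and it may not be estimable for rare contacts in small groups. For illustration, at an assumed 0.02 hospitalizations per 8 weeks, 100 low-risk clients expect 2 per window. With Poisson counts, the chance that at least one window is empty is 1 − (1 − e⁻²)² ≈ 25%. That is why the variance-robust test should carry the risk-group comparison.

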## Abstract

**Introduction:** Social-distancing due to COVID-19 has led to social isolation, stress, and mental health issues in older adults, while overwhelming healthcare systems worldwide. Telehealth involving phone calls by trained volunteers is understudied and may be a low-cost, scalable, and valuable preventive tool for mental health. In this context, from patient participatory volunteer initiatives, we have adapted and developed an innovative volunteer-based telehealth intervention program for older adults (TIP-OA).

**Methods and analysis:** To evaluate TIP-OA, we are conducting a mixed-methods longitudinal observational study.

**Participants:** TIP-OA clients are older adults (age ≥ 60) recruited in Montreal, Quebec.

**Intervention:** TIP-OA volunteers make weekly friendly phone calls to seniors to check in, form connections, provide information about COVID-19, and connect clients to community resources as needed.

**Measurements:** Perceived stress, fear surrounding COVID-19, depression, and anxiety will be assessed at baseline, and at 4- and 8-weeks. Semi-structured interviews and focus groups will be conducted to assess the experiences of clients, volunteers, and stakeholders.

**Results:** As of October 15th, 2020, 150 volunteers have been trained to provide TIP-OA to 305 older clients. We will consecutively select 200 clients receiving TIP-OA for quantitative data collection, plus 16 volunteers and 8 clinicians for focus groups, and 15 volunteers, 10 stakeholders, and 25 clients for semi-structured interviews.

**Discussion:** During COVID-19, healthcare professionals' decreased availability and increased needs related to geriatric mental health are expected. If successful and scalable, volunteer-based TIP-OA may help prevent and improve mental health concerns, improve community participation, and decrease healthcare utilization.

**Clinical Trial Registration**: ClinicalTrials.gov NCT04523610; https://clinicaltrials.gov/ct2/show/NCT04523610?term=NCT04523610&draw=2&rank=1

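### The week-4 scores are collected but are not an analysed visit in either PSS analysis, and no analysis of PSS is named as primary

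*Protocol article*

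**What the plan says.** - **Visits.** Under Client Quantitative Outcome Measures: "All primary and secondary outcomes will be assessed over the phone at baseline, 4-, and 8-weeks (primary study endpoint". The Abstract agrees: the scales "will be assessed at baseline, and at 4- and 8-weeks".
- **First analysis of PSS.** Under Quantitative Analysis: "A within-subjects repeated measure analysis of variance (ANOVA) will be conducted for the PSS (primary outcome". Its stated purpose is "to assess differences in measures between baseline and the 8-week follow-up between groups with different baseline risk", so it uses two visits and compares low, medium and high risk.
- **Second analysis of PSS.** In the same section: "Linear mixed effect regression models, adjusting for age and sex, will analyze the effect of TIP-OA on all outcomes". These outcomes are described as "collected at baseline and 8-week follow-up", again two visits.
- **Missing data.** "We will use LOCF to handle missing data that results from study attrition". The sentence follows the ANOVA and ANCOVA text. The article does not say whether the rule also feeds the mixed models.
- **Other PSS analyses.** ANCOVAs, larger mixed models with variable selection, and subgroup comparisons are each introduced as additional. None of the analyses is called primary, supportive or sensitivity.

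**The concern.** Two things need fixing.

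**Week 4.** The article lists the visits it will analyse and leaves out one that it collects, so this is not detail that a condensed article has merely omitted. In a cohort with no control group, the estimated change depends directly on how clients lost before week 8 are handled. A client who leaves after week 4 has a score taken just before leaving. A two-visit likelihood model ignores that score. LOCF uses it, but as if it were the week-8 value. A three-visit likelihood model uses it to predict week 8.

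**No deciding analysis.** The time effect of the ANOVA and the time effect of the age- and sex-adjusted mixed model both address baseline-to-week-8 PSS change. If the two treat missing scores differently, they can give clearly different answers for the one primary outcome, and the choice would then be made after the data are seen.

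**Working it through.** **No figure of the plan to reproduce.** The article gives 200 clients, justified by precedent, with no effect size, SD, correlation or dropout rate. All such inputs below are assumptions.

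**1. Why week 4 matters under dropout.** Assume correlations of 0.7 (baseline, week 4), 0.7 (week 4, week 8) and 0.55 (baseline, week 8). Given baseline, the partial correlation of week 4 with week 8 is

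(0.7 - 0.7 × 0.55) / √[(1 - 0.7²)(1 - 0.55²)] = 0.315 / √(0.51 × 0.6975) = 0.315 / 0.596 = 0.53.

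If leaving after week 4 depends on the week-4 score, baseline alone does not account for the loss. A model with all three visits does.

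**2. Size of the bias.** Simulation with N = 200, SD 8, the correlations above, 26-29% missing at week 8, logistic dropout driven by the last observed score, and half of any true change present by week 4:

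| Dependence of dropout on last score | Two-visit likelihood, true change 0 | LOCF, true change -3.0 | Three-visit likelihood |
|---|---|---|---|
| None | 0 | about -2.4 | essentially unbiased |
| Log-odds 0.4 per SD | -0.18 | between the two ends | essentially unbiased |
| Log-odds 0.8 per SD | about -0.35 (up to -0.36) | about -1.9 | essentially unbiased |

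The largest two-visit bias is 0.36 / 8 = 0.045 SD. Against a standard error of 0.618 it is 0.36 / 0.618 = 0.58 of one SE. With no true change, LOCF errs the other way, by up to about +0.5.

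**3. Check on LOCF by formula.** If dropout is unrelated to the scores, with cumulative loss d4 and d8 and half the change present by week 4, the share of the true change recovered is (1 - d8) + 0.5(d8 - d4).

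- 5%/15%: 0.85 + 0.05 = 0.90, so -3.0 becomes -2.70.
- 10%/25%: 0.75 + 0.075 = 0.825, so -2.475.
- 10%/30%: 0.70 + 0.10 = 0.80, so -2.40.

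The last line agrees with the -2.4 in the table. Stress-driven dropout lowers it further.

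**4. How far the analyses can part.** In one scenario (27% missing, true -3.0) the two-visit mixed model on observed data gave -3.26, LOCF gave -1.93 and the three-visit model -3.01. The first two differ by 3.26 - 1.93 = 1.33 points on the same clients.

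**5. Precision.** In these simulations the three-visit SE is about 1-3% smaller than the two-visit SE (for example 0.618 to 0.604, and 0.604 / 0.618 = 0.977). A separate generalised-least-squares calculation used random dropout of 5%/15% to 10%/30% and adjacent-visit correlations of 0.5 to 0.8. It gives variance ratios of 0.991 down to 0.925, a reduction of about 1% to 7.5%. With no dropout the ratio is 1.00.

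**6. Error rate.** If either of two tests at 0.05 could support the PSS claim, the error rate is at most 0.05 + 0.05 = 0.10. It would be 1 - 0.95² = 0.0975 if they were independent. These two use the same scores and are positively correlated, so the true figure is lower.

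**The case against.** **Week 8 is the stated endpoint, so a baseline-to-week-8 contrast is legitimate.** This stands. The choice of endpoint is not the fault, and a three-visit model reports the same contrast. Without dropout, adding week 4 gains nothing for it.

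**Week 4 is not thrown away.** This also stands in part. Under LOCF a client lost after week 4 would presumably have that score carried forward. It would then serve as a stand-in for week 8 rather than as an observation at week 4.

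**The two analyses answer different questions.** The study objectives separate the effect on outcomes from the comparison by baseline risk. The ANOVA is worded for the second and the mixed model for the first. A reader might infer two rival primary analyses, and the text does not go that far. What remains is that both are applied to the same outcomes, their time effects overlap, and the article never says which one decides.

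**The plan does not necessarily produce a false improvement.** A reader might infer from the two-visit bias that it would. The documents do not support this, because they leave open whether LOCF feeds the mixed model. If it does, the error runs the other way and a real benefit is understated.

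**The figures rest on assumptions.** Correct. The two-visit bias is small, and it is zero if dropout is unrelated to stress.

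**Conclusion.** The point holds as a matter of text: three visits are collected for the four scales, two are analysed, and no PSS analysis is designated primary. The numerical consequence is conditional on the assumed SD, correlations, dropout and time course. The two-visit likelihood bias runs from 0 to about -0.36 points, which is modest. The LOCF shortfall is larger, at 0.6 to 1.1 points on a true change of -3.0 (3.0 - 2.4 and 3.0 - 1.9). The direction of error in the study cannot be stated, because the reach of the LOCF rule is not fixed. The main gain from week 4 is protection against dropout bias; the gain in precision is slight.

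The point does not extend to mental healthcare utilization. That is counted over the 8 weeks before baseline and the 8 weeks of follow-up, so it has no week-4 value to add. Nor does it call for a multiplicity adjustment across the secondary outcomes. The change should be made before the data are analysed.

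**What to change.** 1. For PSS, the COVID Fear Scale, PHQ-9 and GAD-7, amend the mixed-model sentence so that it covers baseline, week 4 and week 8. Enter visit as a categorical effect.
2. State that this model is fitted to the observed scores without LOCF.
3. Name its baseline-to-week-8 contrast as the primary analysis of PSS.
4. Label the risk-group ANOVA, the ANCOVAs and the models with selected covariates as secondary.
5. Keep utilization as a comparison of its two 8-week windows.

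The cost is a change of wording and slightly more modelling work. The week-4 scores are already being collected.
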